# Multimodal neuroimaging protocol to explore the neural mechanisms of Tiao Shen Li Yan acupuncture in post-stroke dysphagia: a randomized sham-controlled clinical trial

**DOI:** 10.3389/fneur.2026.1764500

**Published:** 2026-06-19

**Keywords:** acupuncture, diffusion tensor imaging (DTI), ischemic stroke, post-stroke dysphagia, randomized sham-controlled trial, resting-state functional MRI (RS-fMRI), structure-function coupling

## Abstract

**Background:**

Post-stroke dysphagia (PSD) remains a frequent and disabling sequela of ischemic stroke, and effective pharmacotherapy is still lacking. Acupuncture has demonstrated significant efficacy in improving swallowing function, yet its neural mechanisms remain unclear. Research into the functional reorganization of brain networks following acupuncture treatment remains insufficient.

**Objective:**

This protocol describes a randomized, single-blind, sham-controlled trial designed to evaluate the clinical effects and central neural mechanisms of Tiao Shen Li Yan acupuncture for PSD, using multimodal neuroimaging with resting-state functional MRI (rs-fMRI) and diffusion tensor imaging (DTI).

**Methods:**

Forty-six PSD patients will be randomized 1:1 to active or sham acupuncture (30 minutes sessions, 5 times per week for 6 weeks). The primary outcomes are rs-fMRI and DTI metrics reflecting functional and structural connectivity changes (ALFF, ReHo, FC, FA, MD). Secondary outcomes include Standardized Swallowing Assessment (SSA), videofluoroscopic swallowing study (VFSS)-based measures, Montreal Cognitive Assessment (MoCA), and Swallowing Quality-of-Life Questionnaire (SWAL-QOL). Twenty healthy volunteers will provide baseline neuroimaging reference data.

**Expected Results:**

The study aims to clarify how Tiao Shen Li Yan acupuncture modulates structure-function coupling in swallowing-related brain networks and promotes functional reorganization of the brain, and to determine whether these imaging biomarkers correlate with clinical improvement.

**Discussion:**

By integrating clinical assessments with multimodal neuroimaging under a rigorous randomized design and by incorporating healthy controls to identify abnormal brain network sites in PSD, this study predefines structure-function coupling metrics and clinical endpoint measures to further explore the neural mechanisms of brain network reorganization underlying acupuncture treatment for PSD. This protocol may provide mechanistic evidence for acupuncture-induced neuroplasticity and support the development of treatment strategies for PSD.

**Trial registration:**

https://www.chictr.org.cn/hvshowproject.html?id=286791&v=1.1, identifier: ChiCTR2400086748.

## Introduction

1

In China, approximately 80% of strokes are ischaemic strokes, which constitute the primary cause of disability and death among adults (1). Dysphagia occurs in 21% to 78% of stroke patients and is associated with aspiration pneumonia and poor functional outcomes (2–4). Despite its clinical relevance, current rehabilitation approaches, such as swallowing exercises, physical therapy, and compensatory maneuvers, offer limited efficacy, and no targeted pharmacological treatment is available (5). Therefore, developing evidence-based, mechanism-informed interventions for PSD remains a critical unmet need in neurorehabilitation.

Acupuncture has been widely applied in post-stroke rehabilitation and has shown encouraging effects in improving swallowing function, with good safety and patient tolerance (5–7). However, the central neural mechanisms underlying its therapeutic effects remain poorly characterized. Traditional Chinese Medicine (TCM) attributes PSD to the “dysfunction of the Yuan-Shen” (primordial spirit), leading to “impaired throat function”. Guided by this theoretical framework, the Tiao Shen Li Yan acupuncture method regulates both systemic and local pathways by stimulating acupoints along the Governing (Du) [e.g., Baihui (GV20), Shenting (GV24)] and Conception (Ren) Vessel [e.g., Lianquan (CV23), Wangu (GB12), Fengchi (GB20), Tianzhu (BL10)]. Preliminary clinical observations from our group have demonstrated improved swallowing performance following this intervention (8), but objective neurophysiological evidence remains limited.

Recent advances in neuroimaging provide powerful tools to explore acupuncture-induced neuroplasticity (9). The spontaneous neural activity and functional connectivity of the brain's internal network can be assessed by resting-state functional MRI (rs-fMRI), and white matter connectivity and its microstructure can be assessed by diffusion tensor imaging (DTI). However, research on the mechanisms of brain functional network remodeling underlying acupuncture treatment for PSD is still insufficient. Rs-fMRI quantifies intrinsic activity (e.g., ALFF, ReHo) and functional connectivity to track network-level functional reorganization after stroke (10, 11). DTI evaluates white-matter microstructure (e.g., FA, MD) and can delineate structural disconnections within swallowing networks (12, 13). In post-stroke dysphagia, neural recovery is thought to involve both functional reorganization of swallowing-related networks and structural remodeling of white-matter pathways. Thus, investigating the interaction between structural and functional networks may provide insights beyond analyses of structural or functional alterations alone (14). Previous imaging studies of PSD have not focused on the interaction between functional and structural remodeling in swallowing-related networks, but only on changes in local activation.

To address this gap, we designed a single-blind, randomized, sham-controlled trial to elucidate the clinical efficacy and neural mechanism of Tiao Shen Li Yan acupuncture in treating PSD. By prespecifying multimodal neuroimaging endpoints—namely, rs-fMRI and DTI—the study aims to characterize how acupuncture modulates brain network organization during swallowing recovery. Specifically, we hypothesize that Tiao Shen Li Yan acupuncture enhances integration within swallowing-related functional networks, promotes microstructural repair of white-matter pathways, and strengthens structure-function coupling, thereby facilitating functional reorganization of brain networks and ultimately improving swallowing function and quality of life in patients with PSD.

This protocol adheres to the SPIRIT 2013 Statement and CONSORT guidelines for clinical trial design and reporting. The findings are expected to provide mechanistic evidence for acupuncture-induced neuroplasticity and to support the development of standardized, evidence-based rehabilitation strategies for PSD.

## Methods and analysis

2

### Registration and trial design

2.1

This single-blind, randomized, sham-controlled trial aims to investigate the therapeutic efficacy and neural mechanisms of Tiao Shen Li Yan acupuncture in patients with PSD.

Forty-six participants will be randomized in a 1:1 ratio to receive Tiao Shen Li Yan acupuncture or sham acupuncture. An additional cohort of healthy volunteers will undergo baseline rs-fMRI and DTI for reference comparisons. Participants will be included only if they fulfill all eligibility criteria and submit written informed consent. Figure 1 shows the research process for this article.

**Figure 1 F1:**
[figure not shown]
Flow chart of the clinical trial procedures.

The trial has been prospectively registered in the Chinese Clinical Trial Registry (ChiCTR2400086748) on 10 July 2024. The trial registration was updated on 30 October 2025 to clarify the outcome hierarchy (rs-fMRI/DTI as the primary outcome; SSA/VFSS-based measures/MoCA/SWAL-QOL as secondary). No other changes were made.

### Study setting and recruitment

2.2

The study will be conducted at Shenzhen Hospital (Futian) of Guangzhou University of Traditional Chinese Medicine. Recruitment will occur across inpatient and outpatient departments via notices and clinician referrals. Baseline demographics and clinical variables will be collected and stored in a secure database under the oversight of the Data Monitoring Committee (DMC), and will remain inaccessible to any person or institution not directly related to this trial.

The study protocol follows the SPIRIT 2013 statement and CONSORT guidelines for interventional clinical trials. Ethical approval has been granted by the Medical Ethics Committee of Shenzhen Hospital (Futian) of Guangzhou University of Chinese Medicine (original approval No. GZYLL (KY)-2023-052; amendment opinion No. GZYLL (KY)-2023-052-02).

### Eligibility criteria

2.3

**Inclusion criteria:** (1) ischemic stroke and dysphagia diagnosed per accepted criteria (15, 16), with Kubota Water Swallowing Test (WST) ≥grade II; (2) aged 30–80 years; (3) stroke onset 2 weeks to 6 months prior; (4) conscious, hemodynamically stable, and able to comply with procedures; (5) written informed consent.

**Exclusion criteria:** (1) coma, Parkinson's disease, or Alzheimer's disease (AD); (2) Severe cardiac, renal, or other organ failure, or critically ill stroke with unstable vital signs. (3) failure to meet the diagnostic criteria for PSD or absence of cerebrovascular disease on neuroimaging; (4) inability to cooperate with evaluation or treatment, or poor adherence; (5) severe psychiatric disorders precluding cooperation with observation or treatment; and (6) contraindications to MRI (e.g., ferromagnetic implants).

### Randomization and blinding

2.4

Randomization will be performed using simple randomization with a random number table. Randomization codes will be sealed in opaque, sequentially numbered envelopes, each containing the corresponding allocation card. Eligible participants will be enrolled in chronological order, and the envelopes will be opened sequentially. A study coordinator will assign participant identification codes and record them in the case report forms. The treating acupuncturists will open the envelopes in sequence and allocate participants accordingly. Baseline details (including name, sex, age, and enrollment date) will be recorded prior to randomization. Opened envelopes will be stored securely in a locked cabinet.

Given the nature of acupuncture, blinding of the acupuncturists cannot be fully implemented. However, outcome assessors, imaging analysts, data managers, and statisticians will remain blinded to allocation in order to minimize potential bias. Blinding procedures will be monitored by the institutional ethics committee. Unblinding will occur only after database lock and completion of primary analyses.

### Interventions

2.5

#### Tiao Shen Li Yan acupuncture group

2.5.1

Points: Baihui (GV20), Shenting (GV24), Yintang (EX-HN3), Fengchi (GB20), Wangu (GB12), Tianzhu (BL10), Lianquan (CV23), Zhaohai (KI6), Lieque (LU7); optional Yuye (EX-HN13), Jinjin (EX-HN12), and posterior pharyngeal wall needling. Acupoint location is shown in Figure 2.

Acupuncture at the EX-HN12/13 points and the posterior pharyngeal wall: The patient opens their mouth, the practitioner uses a sterile disposable acupuncture needle (0.30 × 75 mm) to perform superficial needling at the EX-HN12/13 points and the posterior pharyngeal wall. The needle is inserted shallowly into the mucosa and lightly tapped to induce mild stimulation and slight bleeding. The needle is not retained.

#### SHAM-controlled group

2.5.2

Same point locations but non-penetrating sham needles with sleeves to avoid skin breach and deqi. Needles will be retained for 20 min per session. For EX-HN12/13 points and the posterior pharyngeal wall, blunt tips will lightly touch the mucosa without bleeding.

Schedule: Treatment will be administered once daily, 5 days per week, for 30 min per session over a total of 6 weeks, and will be delivered by licensed acupuncturists with more than 5 years of experience who have been trained in the study protocol.

#### Healthy control group

2.5.3

A cohort of 20 healthy volunteers will undergo the identical rs-fMRI and DTI acquisition protocols. These baseline reference data will enable precise identification of PSD-specific alterations in brain functional networks and white-matter structure.

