#### Primary outcome

2.7.2

Derived imaging metrics will be calculated from the acquired rs-fMRI and DTI data as described below. The primary neuroimaging outcomes are defined as the changes from baseline to week 6 in prespecified rs-fMRI metrics (ALFF, ReHo, and FC) and DTI metrics (FA and MD). In addition, 20 healthy controls will undergo baseline rs-fMRI and DTI examinations to provide a reference for PSD-specific neuroimaging alterations.

Rs-fMRI: Rs-fMRI is extensively utilized to probe the neural mechanisms of PSD. The rs-fMRI markers include amplitude of low-frequency fluctuations (ALFF), regional homogeneity (ReHo), and functional connectivity (FC), which can be used to reflect brain function in patients with PSD. However, existing research primarily emphasizes activation in localized brain regions, with insufficient exploration of acupuncture's effect on functional networks in PSD patients (17).

Therefore, we employed rs-fMRI to analyze brain functional network connectivity, aiming to further clarify the central mechanisms underlying acupuncture treatment for PSD.

ALFF: ALFF reflects the local activity level of specific brain regions by calculating signal strength in the 0.01–0.1 Hz frequency band. It is commonly utilized to explore activation patterns in various brain areas, facilitating our understanding of functional changes across different regions following a stroke, particularly those related to swallowing (18).ReHo: ReHo can capture local coherence changes within swallowing-network nodes (e.g., insula, M1, SMA) in PSD by measuring the temporal synchrony between a given brain region and its adjacent voxels, thereby assessing the consistency of neuronal activity within that region (19).FC: Functional connectivity assesses the interconnections between brain regions based on correlations in temporal sequences. Seed-based analysis (e.g., bilateral insula, M1 orofacial area, SMA) and independent component analysis (ICA) employ data-driven methods to capture broader network-level modulation. Evaluating overall connectivity patterns enhances our understanding of how acupuncture may improve neural network function in PSD patients (20, 21).

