Statistical Modeling: For clinical outcomes and imaging metrics, linear mixed-effects models will be employed to assess within-subject change (baseline vs. week 6) and between-group differences (acupuncture vs. control), while adjusting for sex, age, stroke severity, and lesion volume (48). Correlation analyses will test associations between rs-fMRI/DTI metrics and clinical improvement in swallowing function (SSA/VFSS-based measures/MoCA/SWAL-QOL scales) (49, 50). This will aid in assessing whether alterations in brain networks correlate with improvements in swallowing function, thereby enhancing the clinical interpretability of imaging findings. Depending on the assumptions of normality and linearity, analyses will use either Pearson's correlation coefficient or Spearman's rank correlation coefficient.

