## Discussion

3

Currently, acupuncture has demonstrated significant efficacy in the treatment of PSD and is recommended in clinical guidelines (16); however, its central mechanisms remain unclear. Previous fMRI-related studies have primarily focused on the activation effects of acupuncture on PSD brain regions, whilst in-depth exploration of the mechanisms underlying functional network reorganization remains relatively limited (51). This study employs multimodal rs-fMRI and DTI to investigate the mechanisms of brain functional network reorganization in patients with PSD treated with Tiao Shen Li Yan acupuncture. To our knowledge, this is the first study to elucidate changes in acupuncture-induced brain functional connectivity patterns and structural alterations in inter-network white-matter pathways, thereby exploring the underlying structure-function coupling mechanisms, while also using healthy individuals as imaging baseline controls to define PSD-specific network alterations. Through objective neuroimaging evidence and clinical data, this study aims to provide crucial support for advancing acupuncture research and clinical practice.

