Therefore, in the present study we explicitly separate primary and secondary analyses. The primary (confirmatory) analyses anchor structure-function coupling tests to a prespecified ROI set that captures core swallowing-related hubs with consistent PSD abnormalities (insula, basal ganglia, frontal cortex, M1, SMA, corona radiata, and S1). The secondary (supportive) analyses extend to larger-scale circuits (DMN, frontal–temporal–sensory–motor, sensory–motor–insular–thalamic, and insula–cerebellum–occipital circuits) and are interpreted as hypothesis-generating.

DTI provides complementary insight into the microstructural substrates of PSD. The severity of white-matter injury—reflected by FA and MD metrics—is closely related to the severity of dysphagia, and adaptive white-matter changes may accompany recovery (59). Stroke is associated with disturbances of both functional and structural networks and with state-dependent reductions in functional-structural coupling (60). Therefore, this study included 20 healthy controls as a baseline reference to identify network sites with PSD abnormalities. Combined rs-fMRI and DTI analyses of SC-FC coupling sensitively index clinical impairment and recovery after PSD (46, 60).

Rs-fMRI studies indicate that acupuncture can activate swallowing-related cortical regions in PSD and enhance activity within central swallowing hubs, thereby promoting functional recovery of the cortical swallowing centers. FNIRS evidence suggests that acupuncture facilitates frontotemporal-sensorimotor network integration (61). However, PSD involves not only widespread cortico-cortical injury but also disruption of cortico-subcortical networks, and the mechanisms of structure-function reorganization remain insufficiently understood (51).

Building on this analysis hierarchy, we will examine whether acupuncture-related changes in structure-function coupling and circuit-level functional connectivity track clinical improvement over the 6-week intervention period, using healthy controls as a baseline reference.

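### The healthy-volunteer comparison cannot show PSD-specific alterations, because every patient has both stroke and dysphagia and no stroke group without dysphagia is included

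*Protocol article*

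**What the plan says.** The claim appears three times in the protocol article. Section 2.5.3 (Healthy control group) states: "These baseline reference data will enable precise identification of PSD-specific alterations in brain functional networks and white-matter structure". Section 2.7.2 (Primary outcome) states: "20 healthy controls will undergo baseline rs-fMRI and DTI examinations to provide a reference for PSD-specific neuroimaging alterations". Section 3 (Discussion) describes the study as "using healthy individuals as imaging baseline controls to define PSD-specific network alterations".

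Two further places give the volunteers the task of locating abnormal sites without using the word specific. One is the Discussion paragraph of the Abstract. The other is a later paragraph of Section 3: "this study included 20 healthy controls as a baseline reference to identify network sites with PSD abnormalities".

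On who is compared, Section 2.3 requires of each patient "ischemic stroke and dysphagia diagnosed per accepted criteria (15, 16), with Kubota Water Swallowing Test (WST) ≥grade II". Section 2.5.3 describes the comparator only as follows: "A cohort of 20 healthy volunteers will undergo the identical rs-fMRI and DTI acquisition protocols". No other non-randomized group is planned.

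**The concern.** A finding is specific to post-stroke dysphagia only if it is absent, or clearly weaker, in stroke without dysphagia. Comparing dysphagic stroke patients with healthy people does not test that. Any difference may come from the infarct and its remote effects, from the swallowing disorder, or from both.

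What is at stake is interpretation. Section 3 plans to read treatment-related change in coupling and connectivity with the healthy group as baseline reference, and it presents the healthy group as part of the study's novelty and as a strength. If a site that is abnormal simply because of infarction is labelled a dysphagia site, later change there will be read as reorganization of the swallowing network. The limitations in Section 3 do not mention this.

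**Working it through.** **1. Group sizes.** Section 2.9 plans 20 per arm, 40 in total, raised by 15%: 40 × 1.15 = 46, which reproduces the stated figure. The healthy group is 20. The article gives no effect size or power for the healthy contrast. The argument in steps 2 and 3 does not depend on these sizes; they enter only in step 4.

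**2. What the contrast estimates.** Let S indicate stroke and D indicate dysphagia, and write the mean of a baseline imaging metric as a + b_S·S + b_D·D.

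| Group | S | D | Mean |
|---|---|---|---|
| Patients (Section 2.3) | 1 | 1 | a + b_S + b_D |
| Healthy volunteers (Section 2.5.3) | 0 | 0 | a |
| Stroke without dysphagia | 1 | 0 | not in the design |

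Patients minus healthy = b_S + b_D. Because S equals D for every participant, only the sum can be estimated. A dysphagia-specific statement needs b_D, and that requires the missing third row. Adding age, sex or any other covariate leaves S and D identical, so it does not help.

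**3. Whether b_S can be taken as zero.** The article says otherwise. Section 3 reports that stroke as such disrupts functional and structural networks and weakens the coupling between them, which are the quantities to be compared.

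**4. Illustration of size.** The documents give no value for b_S, so a range is assumed, with b_D set to 0. For a two-sample t-test at two-sided 0.05 (the level in Section 2.11.2), the noncentrality is d × sqrt(n1·n2/(n1 + n2)). For 46 versus 20 this is d × sqrt(920/66) = 3.73·d.

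| Assumed general stroke effect (SD) | P(significant), 46 vs 20 | P(significant), 40 vs 20 |
|---|---|---|
| 0.2 | 11.4% | 11.1% |
| 0.5 | 45.2% | 43.5% |
| 0.8 | 83.7% | 81.9% |
| 1.0 | 95.7% | 94.8% |

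In every row the true dysphagia effect is zero, yet each significant result would be called PSD-specific. These are per-metric figures without multiplicity correction. The FDR and Bonferroni steps in Section 2.11.1 would lower them, but those steps guard against the null of no difference between the groups. They do not guard against attributing a real difference to the wrong cause.

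**5. Covariates.** The mixed model in Section 2.11.1 is stated for "between-group differences (acupuncture vs. control), while adjusting for sex, age, stroke severity, and lesion volume". It cannot be carried over unchanged to the healthy contrast, because stroke severity and lesion volume do not vary meaningfully among people without a stroke.

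**The case against.** The strongest reply is that the healthy data are only a reference. The primary outcomes are changes from baseline to week 6 compared between randomized arms. The primary ROI set is fixed in advance from published work, not chosen from the healthy comparison. Section 2.11.1 already plans to correlate imaging metrics with clinical improvement, which does not involve the volunteers. All of this is correct, and it confines the problem to how the patient-versus-healthy contrast is labelled and interpreted. It does not rescue the label. The planned correlations are also not a substitute for an adjusted analysis of dysphagia severity at baseline.

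Two stronger readings are tempting, and the documents support neither.

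- A reader might infer that the volunteers are unmatched and the contrast unadjusted for age. The patient criterion is "aged 30–80 years", and the article states no age range, matching rule or covariates for the volunteers. But silence in a journal article is not evidence that the full protocol or analysis plan has none. Any figure for age bias would rest on an assumed age gap and an assumed correlation with age. The stroke argument also stands even with perfect age matching.
- A reader might infer that the trial's treatment comparison is compromised. It is not, because it does not use the healthy data.

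**Conclusion.** The claim is wrong as written. The healthy contrast can show how stroke patients with dysphagia differ from healthy adults, but it cannot show which differences belong to dysphagia. This follows from the stated eligibility and groups alone, without numerical assumptions, and no later analysis plan can change it while there is no comparator with stroke but without dysphagia.

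The share of any observed difference due to dysphagia is not identifiable, anywhere from none to all. The 11% to 96% range in the table rests on assumed stroke effects of 0.2 to 1.0 SD and an uncorrected 0.05; it illustrates the risk and does not predict it. The consequence is moderate: a repeated interpretive claim is unsupported, while the randomized comparison and the primary ROI set stand.

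**What to change.** 1. In Sections 2.5.3 and 2.7.2 and the opening paragraph of Section 3, replace the PSD-specific wording with: alterations in stroke patients with dysphagia relative to healthy adults. Drop the word precise in Section 2.5.3.
2. In the Abstract's Discussion paragraph and the later paragraph of Section 3 on healthy controls, qualify the abnormal sites in the same way.
3. Add to the limitations in Section 3 that these differences cannot be attributed to dysphagia rather than to stroke.
4. Base any dysphagia-related interpretation on a regression, among patients only, of baseline imaging metrics on baseline SSA and PAS, adjusted for age, sex, stroke severity and lesion volume. SSA and VFSS are scheduled at baseline (Figure 3 legend), FLAIR is acquired for lesion delineation (Section 2.7.1), and the covariates are already planned (Section 2.11.1). It should be called supportive: it remains observational, rests on at most 46 patients, and concerns severity among people who all have dysphagia.
5. State that the healthy contrast is adjusted for age and sex. This is sensible in itself but does not make the contrast specific.

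The cost is some rewording, one extra supportive analysis on data already being collected, and a more modest claim. Section 2.15 reports that no primary outcome analysis had been done at submission, so the change can still be made in advance. Matching of volunteers is not requested: planned recruitment ended on 31 December 2025, and the article does not say whether any volunteers remain to be enrolled.
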